### The adjudicated final diagnosis

Both components of the primary outcome are adjudicated by two independent cardiologists. Interrater reliability is assessed by documenting the number of patients with mismatch in the final diagnosis of AMI by the 2 adjudicating cardiologists, which requires involvement of a third cardiologist. AMI will be defined according to the Fourth Universal Definition of Myocardial Infarction, which requires evidence of myocardial necrosis in addition to ischemia (as shown through ECG changes, positive findings of stress ECG, myocardial perfusion, coronary CTA or CAG) [25]. In brief, necrosis will be diagnosed based on an increase or decrease (20% relative increase) in the hs-cTnT concentration with at least 1 measurement above the 99th percentile of the normal reference range at a level of assay imprecision near 10%. Type I MI is characterized by atherosclerotic plaque rupture, ulceration, erosion, or dissection, with the resulting intraluminal thrombus in one or more coronary arteries leading to myocardial necrosis (any hs-cTnT concentration above 14 ng/L, with an increase and decrease in the hs-cTnT concentration where serial testing is available). Type II MI is defined as myocardial necrosis in which a condition other than coronary plaque instability contributed to an imbalance between the myocardial oxygen supply and demand (e.g., coronary artery spasm, coronary embolisms, hypertension, or hypotension). All other patients will be classified as “no AMI” in this analysis. Unstable angina will be diagnosed in patients with typical ischemic symptoms at rest or minor exercise with no evidence of acute myocardial necrosis (normal or elevated hs-cTnT levels without any relevant change during serial sampling). Vasospastic angina pectoris was diagnosed in patients with no obvious coronary stenosis, in which an ECG revealed ST elevation, or there was angiographic evidence of a coronary artery spasm that was released after the intracoronary administration of 1 mg of nitroglycerin [18, 26, 27]. Noncardiac chest pain was diagnosed based on the absence of findings from laboratory tests, ECG, and chest radiography at the 30-day follow-up.

### Adherence

The principle investigator have regular web meeting (every the other month) with local PI and their colleagues.

### Study governance

The steering committee of emergency physicians, emergency and cardiology nurses, cardiologists, implementation experts, and clinical pathologists with representation from each of the participating hospitals is providing oversight to the study. Data management is centralized at Novelle PACE Inc. (Tokyo, Japan). REDCap (Research Electronic Data Capture) will be used as electronic case report form (eCRF) to collect and manage study data. All local and server databases will be secured with password-protected access systems, access logging, and encryption. Members of the endpoint committee have access to the patient information via encrypted server access and encrypted hard drives. A clinical event adjudication committee, independent of the study management team, is providing blinded evaluations (events deidentified for treatment arm, hospital, and patient details) of all components of the primary endpoint, including index (within 12 h of initial presentation) and subsequent MI. All study-related information will, until collection, be stored securely at the study sites in areas with limited access. After collection and entry, laboratory specimens, reports, and data collection forms will be identified by a coded participant ID number to maintain participant confidentiality. Forms and any other listings that link participant ID numbers to other identifying information will be stored separately from study records with the participant ID number.

### Statistical analyses

Continuous variables will be presented as the mean (standard deviation) or median (interquartile range [IQR]), and categorical variables will be presented as numbers and percentages. The 30-day incidence of MACEs will be analyzed using generalized linear mixed models after adjusting for background information and seasonal effects. The clustering effect by hospital will be considered in this analysis as a random effect. The binomial distribution and identity link will be used to directly estimate the absolute differences in MACE incidence between 0/1-h algorithm care and usual care patients. The main model will include conditions (control or intervention) and steps (time periods) as categorical variables and hospitals as clusters. Differences in MACEs with a 1-sided 95% CI will be estimated in order to evaluate non-inferiority. The non-inferiority margin is preset at 1.5%. The sensitivity and negative predictive values (NPVs) for MACEs in the rule-out group and the specificity and positive predictive values (PPVs) for MACEs in the rule-in group will be calculated. Multiple imputations will be used to handle missing data. The statistical analyses will be performed using the SAS software program, version 9.4 (SAS Institute, Cary, NC, USA), and R version 4.0.3 (R Foundation for Statistical Computing, Vienna, Austria).

### Auditing

This study does not have a dedicated research audit department. There is no independent Trial Auditing Committee. Instead, the research team reviews recruitment rates every 2 weeks and meets on every 2-month basis to discuss key milestones as well as the conduct of the research, ensuring the integrity of the protocol and conduct of the study.

### Protocol amendment

Any significant amendments to the study protocol will be provided to and approved by the Ethical Review Board of Juntendo University Nerima Hospital before implementation. If approved, these changes would have to be reported in the trial register.

### Ancillary and post-trial care

There is no ancillary post-trial care or compensation. Patients are enrolled in routine therapy during the study duration.

### Dissemination policy

The trial results will be published in a peer-reviewed journal. The results will also be presented at scientific conferences. A popular science summary of the results will be posted online for laymen and study participants. An anonymized data set as well as statistical code used to analyze the data will be published in a data repository on open science framework.

### Patient and public involvement

A patient review panel was consulted throughout the trial program and provided input on the educational advice provided to clinicians after the introduction of the new pathway. Patients were not involved in the conception or design of the trial.

### Cost-effectiveness analyses

These analyses will be performed in six hospitals in Japan, Taiwan, and Thailand, only, as the remaining centers participating in this study lack a system for conducting cost analyses.

#### Japan

The diagnosis procedure combination (DPC; flat-fee payment system) is the bundled payment system of medical fees for acute inpatient medical care in Japan [28].

The bundled payment for each hospitalization will be calculated according to the codes in the International Classification of Diseases 10th revision (ICD-10) and the coefficient for each facility. The DPC database contains six categories of diagnoses, each with a limited number of recordable diseases. One diagnosis each is coded for the “main diagnosis,” “admission-precipitating diagnosis,” “most resource-consuming diagnosis,” and “second-most resource-consuming diagnosis.” A maximum of 4 diagnoses (10 diagnoses from 2016) each can be coded for “comorbidities present at time of admission” and “conditions arising after admission.” All procedures performed during hospitalization and outpatient management are recorded according to the Japanese fee schedule for reimbursement. The DPC component corresponds to the so-called “hospital fee,” including the basic hospital charge, pharmaceuticals, injections, laboratory examinations, and other related expenses, and is paid on a per-day payment scheme. The fee-for-service (FFS) component corresponds to the charges for surgical procedures, angiography, and other related expenses. The revenue equals the sum of the DPC and FFS components. “Material costs” include the costs of pharmaceuticals and medical materials. The total hospitalization costs are calculated as the sum of bundled payment and FFS, without the food fee [29]. The data will be anonymized and not include any information that might be used to identify individuals or hospitals. Each patient will have an identifier specific to the hospitals, with all patients regarded as a single individual, regardless of having both inpatient and outpatient data. The DPC data used for payments include patient demographics and select clinical information, admission and discharge statuses, diagnoses, surgeries and procedures performed, medications, and special reimbursements for specific conditions. In this study, the DPC data will be evaluated from admission to the 30-day follow-up period. The data will be excluded if patients receive care from a non-cardiology department.

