#### Secondary outcome measures

The following predefined secondary outcomes are considered:The proportion of patients managed as outpatients in order to quantify the efficacy of the investigated approaches in both arms.The time from ED presentation to discharge in outpatients. The ED dwell time is derived from a common electronic patient record system used across all participating sites and is calculated as the time of the medical examination between the start time (sign-in time: defined as first medical contact with a MD or the triage nurse) and the end time (sign-off time: defined as the time when the attending physician has finished all medical procedures in the ED, including charting, with the patient to ready to leave the examination room either to be discharged or transferred to a different unit/ward within the hospital).All-cause mortality (cardiovascular death and non-cardiovascular death) and new myocardial infarction (type 1 or 2) within 30 days after the index presentation.Incidence of any cardiac revascularization within 30 days after the index presentation.Incidence of ED representation or hospitalization for unstable angina within 30 days after the index presentation.Costs for healthcare resource use within 30 days following the index ED presentation are calculated based on each country’s guidelines and cost tables for hospitals. Different costs are used for academic and general hospitals. For each patient, the costs are calculated based on the observed number and type of healthcare resources used.Incidence of cardiac examinations (e.g., stress testing or coronary angiography) within 30 days after the index presentation. Adherence to the intervention condition (the 0/1-h algorithm) was evaluated.

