### Study purpose

There are three complete randomized controlled trials that have been performed in this area. Two are from UK [24, 37], and the other is from Australia [10]. To expand the application of the 0/1-h algorithm in Asian countries, we intended to conduct a prospective, stepped wedge, cluster-randomized controlled approach, which will help evaluate the overall safety and efficacy of this novel approach. Asian countries are highly relevant as they represent a very large population with heterogenous medical settings. In general, when assessing novel diagnostic approaches with the potential to improve efficacy, clinicians always require evidence that safety of such a decision rule is non-inferior to standard of care. We also intend to compare the ED dwelling time as well as medical costs among Japan, Thailand, and Taiwan as a secondary endpoint. We hypothesize that the implementation of the 0/1-h algorithm has the potential to achieve an improved cost performance by the shortened ED dwelling time as well as the avoidance of unnecessary admissions or costly downstream cardiac examinations.

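### Japanese costs are counted from admission while the cost outcome runs from the index ED presentation, so a patient sent home has no defined cost start or total

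*Protocol article*

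**What the plan says.** The protocol article (Secondary outcome measures) sets the start and length of the cost outcome: "Costs for healthcare resource use within 30 days following the index ED presentation are calculated". It also sets the unit of analysis: "For each patient, the costs are calculated based on the observed number and type of healthcare resources used".

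The Japan subsection of Cost-effectiveness analyses describes the data source, the DPC, which "is the bundled payment system of medical fees for acute inpatient medical care in Japan". It defines one total: "The total hospitalization costs are calculated as the sum of bundled payment and FFS, without the food fee". It gives the window as: "In this study, the DPC data will be evaluated from admission to the 30-day follow-up period". The same subsection also says: "All procedures performed during hospitalization and outpatient management are recorded according to the Japanese fee schedule for reimbursement". It treats a patient's inpatient and outpatient data as belonging to one individual.

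Under Study purpose, the expected economy comes from shorter ED stay and from "the avoidance of unnecessary admissions or costly downstream cardiac examinations".

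**The concern.** The outcome definition and the Japanese costing rule start the clock at different points. For an admitted patient the gap is the ED work-up before admission. For a patient discharged from the ED there is no admission at all, so the Japanese rule gives neither a start date nor a total.

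These are the patients through whom the intervention is expected to save money, and the proportion managed as outpatients is itself a secondary outcome. A cost clock tied to admission depends on an event after allocation that the 0/1-h algorithm is meant to make rarer. If that event also decides who enters the cost data, or what cost they carry, the comparison between conditions can be distorted systematically.

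**Working it through.** The article states no cost figures, so there is nothing to reproduce. The check is a comparison of the texts, followed by an illustration with assumed units.

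**1. The rules side by side**

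| | Outcome definition | Japan | Taiwan | Thailand |
|---|---|---|---|---|
| Start | Index ED presentation | Admission | No admission start stated | No admission start stated |
| Unit | Each patient | Not restated | Not restated | Each participant |
| Total | Resources used | Hospitalization: bundled payment + FFS | All medical costs | Itemised drugs, laboratory and services |

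Only Japan is tied to admission.

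**2. Patients traced through the Japanese rule, read literally**

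- Admitted: bundled payment and FFS count; ED work-up before admission does not.
- Sent home, never admitted: no start and no defined total. The outpatient charges are said to be recorded, but neither the stated window nor the stated total says that they count.

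**3. Size, with assumed inputs**

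Assume an admitted patient costs A = 100 units and a patient sent home costs O = 5 to 20. The admitted share falls by 10 points, from p_c to p_i (50 to 40%, 40 to 30%, or 30 to 20%).

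- All patients from presentation: saving = (p_c − p_i)(A − O). This is 0.10 × 95 = 9.5 at O = 5, and 0.10 × 80 = 8.0 at O = 20.
- Patients sent home entered as zero: saving = (p_c − p_i)A = 0.10 × 100 = 10. The overstatement is 0.10 × O = 0.5 to 2.0 units per patient.
- Patients sent home omitted: mean among admitted = 100 in both conditions, so apparent saving = 0.

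Now assume that the avoided admissions are cheaper, at 50 units each, while the rest stay at 100. The admitted-only mean under usual care is (p_i × 100 + 0.10 × 50) / p_c:

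| Admitted share | Usual care | 0/1-h algorithm | Apparent increase |
|---|---|---|---|
| 50 to 40% | 45/0.50 = 90.0 | 100 | 10.0 |
| 40 to 30% | 35/0.40 = 87.5 | 100 | 12.5 |
| 30 to 20% | 25/0.30 = 83.3 | 100 | 16.7 |

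The saving over all patients in each row is 0.10 × (50 − 5) = 4.5 units at O = 5, or 0.10 × (50 − 20) = 3.0 at O = 20. Zero entry would show 0.10 × 50 = 5.0.

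**4. A limit on the zero-entry figure**

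Step 3 counts the ED work-up of admitted patients inside A. If the admission start removes that too, and it costs e in both conditions, the overstatement shrinks to (p_c − p_i)(O − e). It vanishes when a patient sent home costs only the ED work-up. What is then lost is any change in ED cost itself, which is one of the expected sources of saving.

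**The case against.** The strongest reply is that the outcome definition governs and the Japan subsection only prices one component. On that view the hospitalization formula shows how an inpatient stay is valued, and the window sentence concerns the DPC data, which come from an inpatient payment system. Outpatient procedures are said to be recorded, and inpatient and outpatient data are treated as one individual's. Limitations describes the DPC as able to capture the whole medical cost during follow-up. Admission may be loose wording for arrival at hospital, and extraction detail often sits in a fuller protocol or analysis plan that is not shown.

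Much of this stands. A reader might infer that an avoided admission becomes a missing record, or that Japanese costs will be compared among admitted patients only. The article says neither; its per-patient wording and the recorded outpatient data point the other way. A reader might also take the sign reversal as a forecast. It needs both an admitted-only denominator, which is stated nowhere, and avoided admissions that are cheaper than the rest. With equal admission costs nothing reverses, and under zero entry the avoided admissions do show as a saving.

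The reply does not remove the conflict. The article states a time origin for Japan that differs from the one in the outcome definition, and nowhere says how outpatient charges enter a patient's total. Having the data recorded makes the repair cheap but does not supply the rule.

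**Conclusion.** The point holds as a contradiction in the stated time origin together with an undefined total for patients sent home. An analyst who followed the Japan subsection to the letter would not produce the outcome defined under Secondary outcome measures.

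Bias is a possible consequence, and its direction turns on an unstated choice. Omitting patients sent home hides the saving (0 against 8.0 to 9.5 units) or, if the avoided admissions are the cheaper ones, reverses it. Entering them as zero overstates the saving by up to 0.5 to 2.0 units per patient. That is 5% to 25% of the saving when all admissions cost the same (0.5/9.5 and 2.0/8.0), and more in proportion when the avoided admissions are cheap. All unit costs and admission shares here are assumptions.

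The scope is one secondary outcome in the Japanese costing hospitals. The primary safety analysis is unaffected.

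**What to change.** Bring the Japan subsection into line with the outcome definition:

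- Start the cost window at the index ED presentation for every enrolled patient at the Japanese costing hospitals, and end it at day 30 from that presentation.
- Define the total as ED and outpatient fee-schedule charges plus bundled payment plus FFS.
- State that a patient who is not admitted carries zero inpatient cost and stays in the analysis with the ED and outpatient charges incurred.

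The cost is a change of wording and a small extra extraction of charges that the article says are already recorded. The Taiwan and Thailand subsections set no admission start and need no change on this point. The Japanese exclusion of patients treated by a non-cardiology department is a separate matter that this change does not settle.

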#### Taiwan

The DPC is the payment system of medical fees for acute patient medical care in Taipei City Hospital. The payment will be calculated according to the medical cost requested from the National Health Insurance program. The database contains cardiologic-related diagnoses. Each patient is coded for the “main diagnosis,” “admission-precipitating diagnosis”, “every comorbidity at every admission,” and “second-most resource-consuming diagnosis.” All procedures performed are recorded according to the Taiwanese fee schedule for reimbursement. The total cost component corresponds to the so-called “hospital fee,” including the basic hospital charge, pharmaceuticals, injections, laboratory examinations, surgical procedures angiography, and other related expenses, and is paid on a per-day payment scheme. The total costs are calculated as the sum of all medical costs, without the food fee, which is recorded in the hospital computer system.

#### Thailand

The cost for each participant will be identified from the hospital electronic database. The total cost will be disaggregated into individual cost items, including drugs, laboratory fees, and service costs, such as interventions, operations, and room costs, incurred at Maharaj Nakorn Chiang Mai Hospital, Faculty of Medicine, Chiang Mai University.

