### Limitations

Our study is associated with several limitations. First, while the study is powered to document non-inferiority in safety of the 0/1-h algorithm compared with standard care, the targeted sample size does not allow to test for superiority in efficacy. Nevertheless, given the real-world design of this study with broad inclusion criteria, observations made within this study will provide important insights into the clinical utility of the 0/1-h algorithm in all-comers. Second, as the primary outcome, we assess the incidence of MACE within 30 days after index presentation in outpatients, which is the most relevant and best accepted measure to quantify safety of any triage algorithm in suspected ACS. However, we cannot comment on outcomes that occur beyond 30 days. Third, only Japan has a national registry named DPC to evaluate a whole medical cost related with the medical service in a following period. Other countries do not have. Therefore, in both Taiwan and Thailand, we will evaluate it in each hospital, individually. In the remaining centers, no data on cost-efficacy will be collected, which could cause some selection bias. Fourth, we cannot comment on the utility of the 0/1-h algorithm in patients with terminal kidney failure on chronic dialysis, because these patients were excluded from the initial studies deriving and validating this algorithm. Thus, patients on chronic dialysis will be excluded also in this study. Fifth, some selection bias may occur due to the need for consent in the intervention arm. Sixth, Juntendo University Nerima Hospital Juntendo University Urayasu hospital, and Tapei city hospital had a history to implement the 0/1-h algorithm. But during the usual care period, second measurement of troponin at 1-h interval will be prohibited.

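### The country cost sections do not deliver the 30-day cost outcome: Taiwan and Thailand count study-hospital costs only, and the Japanese window starts at admission

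*Protocol article*

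**What the plan says.** Under Secondary outcome measures, the article defines the outcome as "Costs for healthcare resource use within 30 days following the index ED presentation". It adds that "For each patient, the costs are calculated based on the observed number and type of healthcare resources used", using each country's guidelines and hospital cost tables. No restriction to the index hospital is stated.

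The Cost-effectiveness analyses section then fixes the source by country:

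- **Thailand.** Costs come from the hospital's electronic database and cover items "incurred at Maharaj Nakorn Chiang Mai Hospital, Faculty of Medicine, Chiang Mai University".
- **Taiwan.** Costs are the sum of medical costs, without food, "which is recorded in the hospital computer system".
- **Japan.** The window is set by the statement that "the DPC data will be evaluated from admission to the 30-day follow-up period". On linkage, "Each patient will have an identifier specific to the hospitals".

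The Limitations section says that "only Japan has a national registry named DPC to evaluate a whole medical cost related with the medical service in a following period", and that Taiwan and Thailand will therefore be evaluated hospital by hospital. The only bias it names is selection, from centres that supply no cost data.

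**The concern.** The outcome and its data sources do not match in three ways.

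1. In Taiwan and Thailand, an ED visit, admission or test at another hospital within 30 days contributes no cost, although the outcome definition would count it.
2. In Japan, the outcome clock starts at ED presentation but the data clock starts at admission. A patient discharged from the ED has no admission, so the text gives that patient no start point. For an admitted patient, the ED phase lies before the stated start.
3. Also in Japan, a patient identifier that belongs to one hospital does not obviously allow a later visit elsewhere to be linked. Limitations nevertheless presents DPC as giving the whole cost of the following period.

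The patients affected are central to the cost question. Under Study purpose, savings are expected from shorter ED stays and from fewer admissions and downstream tests, so ED-discharged patients carry much of the hypothesis. Lower medical cost is also put forward in the Abstract's conclusions and in the Conclusion. What is at stake is whether the analysis can support a statement about total healthcare cost or only about cost at the study hospital.

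**Working it through.** The article gives no cost figure, cost variance or expected saving, so there is no planned number to reproduce. The check has two parts.

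**Part 1: definition against source**

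| | Start of window | Care at other hospitals |
|---|---|---|
| Outcome definition | Index ED presentation | Not excluded |
| Thailand | Not restated | Excluded explicitly |
| Taiwan | Not restated | Not in the source (hospital system; Limitations confirms hospital-level costing) |
| Japan | Admission | Unclear: hospital-specific identifier against a whole-cost claim |

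Taiwan and Thailand have one hospital each. The article speaks of six costing hospitals in Japan, Taiwan and Thailand. If that is the total, index-hospital costing is established for 2 of 6 sites (33%). If the six are the Japanese hospitals alone, it is 2 of 8 (25%).

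**Part 2: effect on the comparison**

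Let eC and eI be the mean uncaptured outside cost per patient under usual care and under the algorithm. Recorded cost is true cost minus e, so

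recorded saving = true saving + (eI − eC).

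The saving is overstated only if eI is greater than eC. The article gives neither quantity. All inputs below are assumptions for illustration: an admission costs 10 units and an ED discharge 1; the discharged share is 0.50 under usual care and 0.65 under the algorithm; half of later admissions occur elsewhere. One later admission then carries an expected uncaptured cost of 10 × 0.5 = 5 units.

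*A. Later admission only in discharged patients, 5% (usual care) and 10% (algorithm).*
- True mean cost: 0.50×10 + 0.50×(1 + 0.5) = 5.75, against 0.35×10 + 0.65×(1 + 1) = 4.80. True saving 0.95.
- eC = 0.50×0.05×5 = 0.125; eI = 0.65×0.10×5 = 0.325. Difference +0.20.
- Recorded saving 1.15, overstated by 0.20/0.95 = 21%. With a quarter elsewhere, the difference is 0.10, or 11%.

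*B. Later admission only in discharged patients, 5% in both conditions.*
- True saving 1.275; eC = 0.125; eI = 0.65×0.05×5 = 0.1625. Difference +0.0375, or 3%.

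*C. Later admission 5% in every patient, including those admitted at the index visit.*
- eC = 0.125 + 0.50×0.05×5 = 0.125 + 0.125 = 0.25.
- eI = 0.1625 + 0.35×0.05×5 = 0.1625 + 0.0875 = 0.25.
- Difference 0: no bias.

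*D. Later admission 8% in patients admitted at the index visit, 5% in discharged patients.*
- eC = 0.125 + 0.50×0.08×5 = 0.125 + 0.20 = 0.325.
- eI = 0.1625 + 0.35×0.08×5 = 0.1625 + 0.14 = 0.3025.
- Difference −0.0225: the saving is understated.

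The result changes sign with inputs that the article does not supply. A and B both give overstatement because they allow no later care to patients admitted at the index visit.

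**The case against.** Several points on the other side have force.

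- **Japan.** A reader might infer that costs are index-hospital-only in all three countries. The documents do not show this. Limitations claims whole-cost capture through DPC, and a hospital-specific identifier makes linkage doubtful without ruling it out. This stands: for Japan the finding is an inconsistency to resolve.
- **ED-only patients.** The Japan section says that procedures in outpatient management are recorded and refers to both inpatient and outpatient data. ED-discharged patients may therefore be costed. This also stands, but the stated window still gives them no start point.
- **Direction of bias.** A reader might infer that the algorithm's savings are overstated because it sends more patients home. Cases C and D show that this does not follow once admitted patients can also have later care elsewhere. The 21% in case A needs later admission among discharged patients to double, which nothing in the article supports.
- **Safety.** It would go too far to say that a missed infarction becomes a saving. Such events belong to the primary outcome, with a 30-day contact and blinded adjudication, and would be reported beside the cost result.
- **Disclosure.** Hospital-level costing in Taiwan and Thailand is declared. This stands in part: the declaration mentions neither omitted outside care nor its possible effect on the comparison, and it does not amend the outcome definition.
- **Wording.** The outcome definition does not expressly say that care at other hospitals is included. That weakens the contradiction, but an unrestricted 30-day resource-use definition reads most naturally as including it.

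**Conclusion.** The mismatch is real and rests on the text alone. Study-hospital costing is explicit for Thailand and, from the data source together with Limitations, clear for Taiwan. In Japan, the start of the window disagrees with the outcome definition, and the coverage of DPC is described in two ways that need reconciling.

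A bias between conditions is possible, but its direction and size are not established. Across the assumed cases, the error in the saving runs from +0.20 to −0.0225 units per patient and passes through zero. These are illustrations, not estimates for this trial.

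The point concerns a secondary outcome and does not touch the primary non-inferiority comparison. It is a minor finding that limits what the cost analysis measures and can conclude.

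**What to change.** 1. **Japan, window.** Start the cost window at the index ED presentation and state that ED-only patients are included.
2. **Taiwan and Thailand.** Define and report the outcome as index-hospital 30-day cost, with no claim of total healthcare savings.
3. **Japan, coverage.** Reconcile the Japan section with Limitations on whether DPC captures care at other hospitals. If it does not, use the index-hospital label there too and withdraw the whole-cost statement.
4. **Outside care.** If use of other hospitals is available from the 30-day contact, cost it with the country tables as a sensitivity analysis only, and only where it was collected in the same way in both conditions.

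The restriction in item 4 matters because of the design. Trial status reports 2124 of the planned 4260 patients (50%) included by 30 September 2022. In a stepped wedge, later patients are mostly under the intervention, so adding outside-care fields midway would record outside costs mainly under the algorithm and confound capture with condition.

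The cost is a narrower conclusion and a small amount of extra analysis. Items 1 to 3 need no new contact with patients.
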